### Treatment Arms

#### Overview

We iteratively developed AB and HEP for the specific needs of older adults with CP-ECD through our previous studies [28,30,31,35]. The control (education only; no skills) is dose-matched and time-matched to the intervention. Both treatment arms are group-based and the intervention is delivered by trained clinicians over 8 weeks (90-min sessions) in addition to patients’ usual care. Participants receive both a paper copy of the structured treatment manual and access to a digital copy through the program website. Both manuals refer to ECD as *memory-related problems* because it was preferred by patients who participated in our qualitative focus groups to develop AB. Participants are encouraged to take notes in the treatment manuals during the sessions and for home practice to promote comprehension and retention. Treatment completers are those who complete a minimum of 6 out of 8 sessions. If participants are unable to attend a session, they are offered a 15-minute makeup with the clinician via Zoom to review missed content and address adherence barriers as needed.

#### AB Intervention

##### Overview

The AB intervention is a multimodal walking program informed by the fear-avoidance model [10]. It integrates relaxation response [52], mindfulness [53], pain-specific cognitive behavioral [54], and operant and physical restoration elements [55]. AB teaches skills to break the *disability spiral* of worsening cognitive, physical, emotional, and social functioning in response to comorbid CP and ECD [9,10]. AB skills include the following: (1) *walking skills* to gradually increase step count through individualized quota-based pacing and goal setting reinforced by a digital monitoring device (Fitbit) linked to valued activities; (2) *mind-body skills* to reduce reactivity to pain or cognitive symptoms through diaphragmatic breathing, body scanning, and mindfulness exercises; (3) *pain-cognition*-*behavior* awareness skills to educate on myths about CP and ECD and understand the disability spiral; (4) *cognitive functioning skills* to develop cognitive compensatory strategies and increase intellectual stimulation; and (5) *social-emotional functioning skills* to cope with stress or setbacks and increase social factors (obtaining social support and decreasing isolation) through self-compassion, gratitude, and acceptance (Table 2). The goal is to provide patients with coping skills to manage pain and develop compensatory strategies to improve their physical, cognitive, and emotional function.

**Table 2 table2:** Session outline for the Active Brains (AB) intervention and Health Enhancement Program (HEP) for older adults with chronic pain (CP) and early cognitive decline.

Session	AB topic	AB skills and session content	HEP topic	HEP session content
1	Taking charge of pain and MRP^a^	Deep breathing	Program overview and CP and MRP	Program goals, understanding CP and MRP, how CP and MRP are connected, and the impact of stress
2	Pace yourself	Mindful breathing and quota-based pacing	The connection among CP, MRP, and physical wellness	The connection between CP and MRP
3	Walk all over pain and MRP	Body scan, mindful walking, and gratitude	Sleep and wellness	Healthy sleeping strategies and cognitive and physical health
4	Mindfulness of pain and MRP	Self-compassion and mindful STOP^b^	Exercise and wellness	Physical exercise, maintaining healthy weight, and tips for becoming active
5	Building brain reserve	Mindful focus	Nutrition 1: the basics	Basic nutrition, portion size and calories, and understanding food labels
6	Staying in the upward spiral	Skill review	Nutrition 2: healthy weight and weight loss	Eating healthy meals and snacks, eating out healthy, and weight loss and BMI
7	Feeling connected with others	Love and kindness mindfulness	Managing your health care for CP and MRP	Communicating with physicians, health diary, medical emergencies, and medication adherence
8	Staying on track and maintaining your progress	Mountain mindfulness	Review of AB	Overview of program content

^a^MRP: memory-related problem.

^b^Stop, Take a breath, Observe with curiosity, Proceed mindfully.

In each session of AB, the clinician and participants review previous session material, discuss home practice, solve barriers, learn educational material, practice program skills and apply them to participants’ daily lives, and create an individualized walking plan (eg, “I will walk to the park once per day while calling family then do housework until I hit my daily goal of 1,200 steps.”) to achieve their step goal. For home practice, participants execute their walking plan, practice skills for at least 5 minutes per day, and log their adherence via daily SMS text messages sent from Twilio [80]. Participants are encouraged to regularly visit the program website to watch videos that explain core concepts (eg, disability spiral and myths about pain) and listen to clinician-guided recordings of mindfulness skills.

##### Fitbit and Quota-Based Pacing

Participants randomized to the AB group receive a Fitbit Inspire [81] to wear from the first session through the 6-month follow-up. Fitbit is a user-friendly and commercially available activity watch that enables participants to monitor (updated step count data on the wrist and Fitbit app) and reinforce (motivating reminders to walk and notifications when step goals are achieved) their daily walking. The AB treatment manual contains written instructions and a tutorial video about wearing, charging, and syncing Fitbit daily. Informed by our internal testing, we instruct participants to wear Fitbit on the nondominant wrist below ActiGraph wGT3X-BT and remove Fitbit during activities with repetitive arm movement (eg, gardening and washing dishes) to prevent step count overinflation. To justify wearing 2 activity watches, we explain that ActiGraph is for the research-grade assessment of step count and Fitbit is to reinforce their quota-based pacing plan.

AB participants are taught to increase their daily step count gradually and safely by following evidence-based guidelines for quota-based pacing [55,82]. The research assistant sets each participant’s initial goal by calculating a truncated average (removing the highest and lowest observation) step count for valid days (≥7 h/d) measured by Fitbit Inspire during the week after session 1. Each subsequent week, the research assistant updates AB participants’ step goal by calculating a weekly truncated average using Fitbit Inspire data synced via the Fitabase web-based platform [83]. AB participants (1) increase their goal by 10% if they achieve their goal, (2) reattempt their goal if they did not achieve their goal for 1 week, or (3) decrease their goal by 10% to 20% if they did not achieve their goal for 2 weeks. Clinicians guide participants in applying AB skills to make the patient’s walking plan noncontingent on CP and ECD symptoms or other barriers to achieving their step goal (eg, weather and time). Research assistants routinely monitor ActiGraph and Fitbit adherence using CentrePoint [84] and Fitabase [83] web-based dashboards, respectively. Participants with 24 hours of nonadherence are contacted for reminders and troubleshooting as needed.

##### Improvements to AB for This Trial

We refined AB based on the results of our pilot feasibility RCT and feedback from participants during exit interviews [35]. First, we streamlined the content in our treatment manual to focus more directly on walking and mindfulness skills. In the updated manual, walking is emphasized as the primary target of AB, and mindfulness is described as a tool to improve coping and support increased activity. Second, we replaced Specific, Measurable, Attainable, Realistic, and Timed (SMART) goals with a simplified walking plan based on feedback from participants stating that the acronym overcomplicated weekly walking goals. Third, we restructured the intervention sessions to incorporate more guided mindfulness practices to support learning before home practice. Similarly, we added structured check-ins at the beginning and summaries at the end of each session to consolidate learning, solve challenges with participants, and encourage skills practice. Fourth, we added information about ActiGraph (for research) and Fitbit (for tracking the daily step goal) to help participants understand the differences between the 2 devices. Fifth, we selected a large font and used a white background with black and dark blue text to maximize contrast, to make the manual more readable for older adults [85]. Sixth, we removed scientific jargon, explained key terms (eg, mindfulness, CP, and ECD) with patient-friendly language, and added figures (eg, to validate that CP-ECD can feel similar to *climbing a mountain* but that gaining AB skills along the way can help). We revised both patient and clinician manuals to ensure that the AB skills are taught to encourage understanding of language in the study outcome measures. Finally, we created animated videos to support the learning of program skills and linked these via a program website throughout the manual.

#### HEP Education Control

Our previous study provides full details about HEP [31]. Briefly, this time-matched and dose-matched attention control accounts for the effects of time spent, feedback, and support from the study clinician and other group members. It consists of lifestyle education consistent with public health recommendations and standards for health promotion (eg, physical activity, sleep, nutrition, healthy weight, and medical appointments). Our team has successfully used HEP as an active control in multiple previous studies [86-88]. We adapted HEP to include population-specific information about CP and ECD symptoms. Consistent with a similar efficacy trial [89], the HEP participants are instructed to journal for 5-10 minutes per day to match the dose of mind-body skill practice in the AB intervention.

### Population-Specific Technology Considerations

#### Overview

Our web-based trial implements several technological solutions to improve the experience of older participants in our study. The treatment arms are delivered via Zoom, which overcomes cost, transportation, and scheduling as important barriers to care in this population. The ActiGraph watch continuously and passively collects step count, which reduces the burden of assessments. Walking goals are reinforced in real time via Fitbit, which addresses difficulty in planning and initiating behavior change with CP and ECD. To bypass ECD symptoms (ie, forgetfulness, distractibility, and difficulty in planning), participants receive SMS text messages to attend sessions, practice program skills, record home practice, and self-monitor pain interference with daily activities. During enrollment, research assistants help AB participants install a shortcut to our program website on their smartphones to easily access clinician-guided recordings of all mindfulness skills. Our pilot study showed that older adults with CP and ECD benefited from and could use these technologies with high feasibility, acceptability, and satisfaction [35].

Our previous study [31] describes our protocol for teaching older adults about technologies based on the National Council on Aging guidelines [90]. During enrollment, research assistants assess participants’ familiarity with technology (eg, experience with Zoom and devices owned), identify individual preferences for remote communication (eg, SMS text, email, or phone), and develop individualized support plans (eg, specific family members who can help). During training sessions, research assistants clarify the value and rationale of each technology, allow time for experimentation, and avoid common pitfalls for communicating with older adults (eg, speaking very loudly or slowly). Our qualitative study has revealed that scheduled, individualized learning sessions; frequent encouragement; and on-call technical support help older participants overcome any initial lack of technological readiness [35].

Informed by *lessons learned* from our pilot RCT, we refined our procedures to further improve participants’ experience with technology. First, we streamlined the written materials in the manual and before-treatment packet on wearing, syncing, and charging the watches. Second, we created a demonstration video about wearing and caring for the watches that participants could easily access on the program website. Third, we increased the involvement of family members and friends to help participants troubleshoot challenges with Zoom, email, and responding to SMS text message surveys. Fourth, participants can receive in-person device setup and training with a research assistant during the baseline period (US $10 is provided for travel). Fifth, participants are encouraged to contact the research assistant with technology-related questions and are offered one-on-one appointments when more extensive troubleshooting or training is required.

#### Treatment Fidelity

We follow the NIH Science of Behavioral Change guidelines to support treatment fidelity [91]. We have developed structured manuals and standard operating procedures that we revised based on the lessons learned after our feasibility pilot study of AB [35] and similar efficacy trials [86]. All study staff meet weekly to discuss participant progress through the study, including session attendance, watch use, home practice adherence, and any deviations from the treatment protocol. All study clinicians are Doctor of Philosophy level clinical psychologists and doctoral-level trainees. The clinicians are directly supervised by the project manager who has extensive training in geriatrics, CP, and mind-body treatments. Following a standardized training protocol, clinicians read selected papers about treating CP and ECD in older adults, listen to audio recordings of the sessions, rehearse the clinician manuals, and colead with a senior clinician before running their first group. Clinicians receive training about adherence to the treatment manual, completion of study forms, assessing participant comprehension, and monitoring the use of skills. During weekly in-person supervision, the clinicians receive feedback about protocol adherence, specific participant or group concerns, and session preparation. All sessions are audio recorded. Clinicians record participant attendance and complete checklists of the content delivered. We will randomly select up to 20% (approximately 40) of these checklists to review. Independent coders will assess each session against a coding scheme to evaluate protocol fidelity, with attention to coder discrepancies. Home practice (eg, step count and skills used) is tracked automatically and reviewed during weekly supervision.

### Data Analytic Plan

#### Power Analysis

Our blinded statistician used SAS (version 9.4; SAS Institute) [92] for the power analysis. Our primary outcome requires clinically important improvements in both functional measures (step count and 6-min walk test) and patient-reported outcome (Patient-Reported Outcomes Measurement Information System Physical Function). Allowing for 20% dropouts, 260 participants recruited (130/group; 104/group completing the study) would provide 92.3% power (Cronbach α=.05; 2 sided) to detect the minimum clinically important difference in step count (1000 steps) [93,94] between the AB and HEP groups in the change from baseline to postintervention assessment. This assumes an SD of 2120, which is the upper 80% confidence limit for the SD observed in our pilot study, as recommended [95]. We also assume 50% correlation between preintervention and postintervention measures. This sample size provides 81.8% power for a difference of 54 meters (the minimum clinically important difference) [96] in the 6-minute walk test (SD 135 based on our pilot data) and >99.9% power for a difference of 5.48 points (minimum clinically important difference) [97] for the Patient-Reported Outcomes Measurement Information System Physical Function score (SD 7.61 based on our pilot data). Assuming a correlation of 0.5 between significant results of step count and 6-minute walk test, the power of the study would be 80.7% (based on simulations) of having a statistically significant result for all 3 coprimary end points.

#### Data Analyses

##### Overview

Our blinded statistician will conduct all data analyses using SAS (version 9.4) [92]. We will estimate treatment-dependent changes in primary (objective, performance-based, and patient-reported physical function) and secondary outcomes (patient-reported and objective cognitive function and emotional function). We will follow the intention-to-treat principle and include all randomized participants in our primary efficacy analyses. Data will be analyzed using a shared-baseline, linear mixed model with fully unstructured covariance among repeated measures. The shared-baseline assumption reflects the true state of the population before randomization and has the benefit of adjusting for chance differences at baseline. Linear mixed models with maximum likelihood estimation are unbiased when data are missing at random, conditional on the observed data. If loss to follow-up is strongly treatment-dependent (relative risk >2), we will use perturbed multiple imputation to assess the robustness of estimates from the primary model if data were missing in not-at-random manner.

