### Assessments and Enrollment

#### Informed Consent and Mailing of Study Materials

After recruiting at least 8 eligible participants (ie, the minimum threshold to start forming a round of groups), research assistants contact each participant to coordinate the informed consent process and mailing of study procedures. A total of 3 weeks before the first AB or HEP session, research assistants conduct 30-minute Zoom (Zoom Video Communications) meetings with participants to: (1) review and sign the electronic consent form, (2) test Zoom and eliminate barriers to web-based participation, (3) download the Timed Walk app [46] (to self-administer the 6-min walk test), (4) schedule the baseline assessments, (5) assess delivery preferences (timing, email, or SMS text) for receiving daily study reminders, (6) collect an address to mail the study materials, and (7) identify a friend or family member to troubleshoot technology if needed. After consent, a research assistant mails the following to each participant: (1) a study welcome letter, (2) a complementary pen and magnet with the study logo and contact information, (3) Repeatable Battery for the Assessment of Neuropsychological Status (RBANS) Update [47] cognitive assessment forms, and (4) a wrist-worn ActiGraph wGT3X-BT (ActiGraph LLC) [48,49] watch and materials (user-friendly instructions and charger) for blinded step count assessment. We provide tablets (to sync watches, respond to surveys, and attend the AB or HEP sessions) to promote equitable participation of older adults who do not own these devices. These participants receive an additional tutorial with a research assistant to set up their tablet. Participants are instructed to leave the study package unopened until the group, baseline assessment Zoom session. So far, all participants have provided informed consent, and all study procedures have been conducted in accordance with our IRB-approved protocol.

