#### Randomization

A week before the first AB or HEP session, research assistants randomize and enroll participants via phone. Participants are randomly assigned in a 1:1 ratio to AB intervention or HEP control to ensure comparability between groups. The unblinded study biostatistician created the randomization schedule with permuted blocks of random sizes and implemented it in REDCap. Randomization is stratified according to ECD type (subjective vs mild cognitive impairment). To maintain single-arm blinding, study staff and materials refer to AB and HEP as AB1 and AB2, respectfully. Without unblinding, research assistants notify each participant about their group assignment, schedule weekly session times, and provide links to the AB or HEP websites. Research assistants review expectations for attending the group sessions, including the following: (1) timeliness, (2) quiet location, (3) respectfulness of others, (4) no multitasking, (5) wearing the watch, (6) having a pen and the manual ready, and (7) responding to daily smartphone surveys to complete home practice. The research assistant mails a printed copy of the program manual to be received by participants before the first group session. Participants in the AB arm receive a Fitbit to wear, starting after session 1 to ensure that step count assessment remains blind in both groups. Participants are considered to be enrolled after completing session 1 of the AB or HEP arms.

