##### Aim 1: Efficacy of AB (Baseline to Posttest Period)

We have already established the feasibility benchmarks of the intervention and control [28,30]; therefore, emphasis of this study is on establishing the efficacy of AB*.* Accordingly, the primary analysis will compare the changes in primary and secondary outcomes (continuous measures) from baseline to posttest period between the randomized conditions. For each outcome, we will compare the effect of AB versus control on changes from baseline to the posttest period using linear contrasts. With 3 coprimary outcomes, no adjustment for multiple comparisons is needed; therefore, we will use 2-sided tests at *P*<.05 to declare the superiority of AB, maintaining an overall 5% type-1 error at our primary postintervention time point. The success of the trial will be declared if participation in AB is associated with statistically significant and clinically important improvement from baseline to posttest period over participation in control based on the 3 physical function outcomes.

We will conduct several sensitivity analyses to ensure that a conclusion about efficacy is robust to possible deviations from the assumptions of the primary model. Baseline parameters will be included to account for chance differences owing to randomization and to explain the sources of variation in response that are independent of treatment group. We will also use a Wilcoxon rank sum test comparing the change in scores between the 2 groups to avoid any parametric assumptions about the data. All secondary outcome measures will be analyzed using the same shared-baseline, linear mixed model and the same secondary sensitivity analyses. Step-down, Bonferroni-adjusted *P* values will be used to control for multiple comparisons regarding the secondary outcomes.

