## Results

The study was funded by the National Institute on Aging in December 2021. The study was approved by the IRB on December 8, 2021. We began recruitment in July 2022. As of March 2023, a total of 201 individuals have been referred and all have been contacted. Of these 201 individuals, we screened 141 (70.1%) and enrolled 37 (18.4%) participants (n=18, 49% in AB and n=19, 51% in HEP) across 4 group cohorts (largest group: n=10, 27%). All (37/37, 100%) participants completed the baseline assessment. Of the 37 participants, 1 (3%) dropped after the first AB session owing to an unrelated psychiatric hospitalization and 1 (3%) dropped after the second HEP session owing to extreme orofacial pain. In the three cohorts (26/37, 70%) that have completed the AB or HEP, 26 (100%) participants completed all 8 of the group sessions (including minimal makeups) and the posttest assessment. Adherence has been high for the Fitbit and ActiGraph watches, with 93.48% (1937/2072) valid days of wear compliance for both devices across the 2 group cohorts. The fourth group cohort is ongoing (9/37, 24%). We plan to complete enrollment by March 2026 and data analyses by February 2027.

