## Discussion

### Significance

Our single-blinded, NIH stage-2 RCT (N=260) is designed to test the efficacy, sustainability, and mechanisms of the AB program in improving self-reported and objective outcomes of physical, cognitive, and emotional function. We anticipate that the results will inform nonpharmacological interventions targeting CP and ECD in older adults. Although most nonpharmacological CP interventions address a discrete pain condition (eg, back pain), we developed our mind-body activity program to address issues that are common across all nonmalignant CP conditions. This is important because most older adults have ≥1 type of pain condition [104]. We are targeting people with both subjective and objective ECD because both are precursors of dementia [1], have similar symptom presentations, and require similar tailoring of skills [105,106]. Our web-based mind-body activity program is grounded in strong theoretical and empirical frameworks [10,52-54], combines mind-body skills with quota-based pacing and engagement in activities of daily living, is delivered in a group format to foster social support, and uses a pacing plan that is tailored to each individual. AB has been iteratively refined using the NIH Stage Model [29] guidelines; follows the Initiative of Methods, Measurement, and Pain Assessment [50] and International Classification of Functioning [51] criteria for CP clinical trials; and has demonstrated excellent feasibility markers and proof of concept [28,30]. The groups conducted so far, although preliminary, show high initial participant retention and adherence to both treatment arms and the study technologies.

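### Both arms are delivered in groups, but the primary model and the power calculation treat participants as independent; if outcomes correlate within groups, the 5% level per endpoint is not kept

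*Protocol article*

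**What the plan says.** Allocation is individual (Randomization): "Participants are randomly assigned in a 1:1 ratio to AB intervention or HEP control". Delivery is not (Treatment Arms, Overview): "Both treatment arms are group-based and the intervention is delivered by trained clinicians over 8 weeks (90-min sessions". Rounds of groups start once enough people are available (Informed Consent and Mailing of Study Materials): "After recruiting at least 8 eligible participants (ie, the minimum threshold to start forming a round of groups". The group is an intended ingredient; the Significance section says the programme "is delivered in a group format to foster social support", and the HEP (education control) section says the control is meant to match the support that comes from the clinician and the other members.

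The model is fixed in Data Analyses, Overview: "Data will be analyzed using a shared-baseline, linear mixed model with fully unstructured covariance among repeated measures". The sensitivity analyses under Aim 1 add baseline covariates and a Wilcoxon rank sum test. The error claim under Aim 1 is: "we will use 2-sided tests at *P*<.05 to declare the superiority of AB, maintaining an overall 5% type-1 error". The Power Analysis section uses 104 completers per arm and gives 92.3% for step count, 81.8% for the 6-minute walk, over 99.9% for PROMIS Physical Function and 80.7% for all three. No group size, ICC or design effect appears in the analytic plan.

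**The concern.** People who share a group, a clinician and eight 90-minute sessions may end with more similar outcomes than people in different groups. An unstructured covariance among a participant's repeated measures does not represent that similarity, and neither do the two sensitivity analyses. If it exists, the variance of the arm difference is larger than the model reports and P values come out too small. The same model serves the secondary outcomes, and under Aim 2 it supplies the noninferiority bound for durability, which would be too tight. A sample size computed for independent people would also give less power to a test that does allow for groups.

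The full analysis plan is not at hand and could contain a group term. But the article does more than stay silent: it states the covariance structure, claims a 5% error rate and gives power to one decimal place.

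**Working it through.** **1. Reproduce the stated power.** Inputs from Power Analysis: 104 per arm, two-sided 0.05, pre-post correlation 0.5. The SD of change is SD × √(2 × (1 − 0.5)) = SD. Noncentrality is δ / (SD × √(2/104)), with 206 degrees of freedom.

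- Steps: 1000 / (2120 × 0.1387) = 3.40, power 92.3% (stated 92.3%).
- Walk: 54 / (135 × 0.1387) = 2.88, power 81.9% (stated 81.8%).
- PROMIS: 5.48 / (7.61 × 0.1387) = 5.19, power 99.9% (stated over 99.9%).
- All three: the article sets a correlation of 0.5 between significant results, so the joint probability is p1·p2 + 0.5·√(p1·q1·p2·q2) = 0.923 × 0.819 + 0.5 × √(0.923 × 0.077 × 0.819 × 0.181) = 0.756 + 0.051 = 0.807. Multiplying by the PROMIS power leaves 80.7% (stated 80.7%).

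The figures therefore rest on a design effect of exactly 1.

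**2. Group size.** Results reports 37 participants "across 4 group cohorts (largest group: n=10, 27"%). If each cohort forms one AB and one HEP group, the mean is 37 / (4 × 2) = 4.6. The text leaves unclear whether the largest group means a cohort or one arm of a cohort, so 8 per group is also shown.

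**3. Design effect and error.** DE = 1 + (m − 1) × ICC. The large-sample two-sided error of the unadjusted test is 2 × (1 − Φ(1.96/√DE)). Example at m = 4.6 and ICC 0.05: DE = 1 + 3.6 × 0.05 = 1.18; 1.96/√1.18 = 1.80; error 7.1%. The ICC values are assumptions.

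**4. Power of a cluster-adjusted test.** Step 1 is repeated with 104/DE per arm, in two ways: (a) on the article's change-score variance, SD²; (b) on the variance of a model that conditions on baseline, as the planned shared-baseline model in effect does, (1 − 0.5²) × SD² = 0.75 SD². All-three power uses the step 1 formula.

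| m | ICC | DE | Two-sided error per test | AB-favouring tail | (a) Walk | (a) All three | (b) Walk | (b) All three |
|---|---|---|---|---|---|---|---|---|
| 4.6 | 0.01 | 1.04 | 5.4% | 2.7% | 80.5% | 79% | 90% | 90% |
| 4.6 | 0.05 | 1.18 | 7.1% | 3.6% | 75.2% | 73% | 86% | 86% |
| 4.6 | 0.10 | 1.36 | 9.3% | 4.6% | 69.1% | 65% | 81% | 80% |
| 8 | 0.05 | 1.35 | 9.2% | 4.6% | 69.4% | 66% | 81% | 80% |
| 8 | 0.10 | 1.70 | 13.3% | 6.6% | 59.3% | 53% | 72% | 69% |

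Without clustering, (b) gives 91% for the walk and 91% for all three. These are design-effect approximations; they ignore the limited degrees of freedom at group level and any clustering by clinician. Column (b) also assumes that the quoted SDs are those of single measurements and that the same ICC applies after conditioning on baseline.

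**The case against.** The strongest reply has four parts.

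- **Power.** A reader might infer that the stated power cannot be reached. The documents do not support that. The published figures belong to a change-score test, while the planned model uses the baseline more efficiently. At the article's own correlation of 0.5 and 4.6 per group, that model exceeds the stated all-three power at ICC 0.01 and 0.05 and misses it by about one point at 0.10. It falls clearly short only when groups are larger and the ICC is high. The step-count SD is also already an upper confidence limit. This part stands.
- **Error.** A reader might infer that the trial's overall error rises to 7% or 9%. It does not. Those are two-sided rates for one endpoint. Success needs all three endpoints, so error when none truly benefits is well below 5%. Inflation reaches the trial's conclusion mainly when the other two endpoints truly benefit, and then only through the AB-favouring tail (2.7% to 4.6% against 2.5% at 4.6 per group). Aim 1 also requires clinically important improvement, without defining it; if that means an estimate at or above the minimum important difference, a false success is rarer still. This part stands as a limit on size. It does not restore the nominal level of each endpoint's test.
- **ICC and group size.** Individual step goals, manualised delivery and individually measured coprimary outcomes could all keep the ICC low. With 20% dropout the analysed group is 4.6 × 0.8 = 3.7, and DE at ICC 0.05 is 1 + 2.7 × 0.05 = 1.135. So the claim must be conditional.
- **The stratum.** The model as described also leaves out type of early cognitive decline (ECD), although "Randomization is stratified according to ECD type (subjective vs mild cognitive impairment"). A reader might count this as a further cause of small standard errors. It works the other way: omitting a prognostic stratum generally makes them too large.

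**Conclusion.** The point holds in conditional form. The plan describes a group treatment whose format is meant to affect participants, fixes a model with no group term, and computes power with a design effect of 1. If outcomes correlate within treatment groups, the unadjusted standard errors are too small and the 5% level per endpoint is not kept. At about 4.6 per group the two-sided error per test is 5.4% to 9.3% for an assumed ICC of 0.01 to 0.10; with no within-group correlation the figures stand as printed.

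For power the conclusion is narrower. The published change-score figures are too high for a cluster-adjusted test at any positive ICC, and the 80.7% has only 0.7 points to spare above 80%. Whether the trial itself is short of power depends on the planned model, which may recover all of the loss.

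**What to change.** Add to the primary model, for every outcome, a random effect for treatment group that acts on the post-baseline visits, with Kenward-Roger or Satterthwaite degrees of freedom, and carry it into the secondary and durability analyses. At 130 per arm and 4.6 per group there would be about 130/4.6 = 28 groups per arm, enough to estimate the term. Restate power for the shared-baseline model actually planned, over a stated range of ICC and group size.

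This changes analysis wording and code, not trial conduct. Group membership must be kept as an analysis variable; since sessions are scheduled and attendance is recorded, it should be recoverable. The price is slightly wider intervals, small if the ICC is near zero.

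As a separate improvement, ECD type can enter as a fixed effect with its visit interaction. It is the randomisation stratum, and adding it costs nothing.
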